#### Data analysis

Our primary analysis will compare the proportion of couples who test for HIV in Igugu Lethu with the proportion of couples in the intervention arm of the Uthando Lwethu study who tested for HIV within 4-months of follow-up, unadjusted, using a chi-square test. We will also compare this cohort’s baseline characteristics with the Uthando Lwethu cohort’s baseline characteristics. If there are substantial differences, the comparison will be adjusted for these characteristics using logistic regression.

We will also consider the proportion of couples taking up each of the other non-HIV tests offered as part of the couples health screening. We will calculate descriptive statistics and apply chi-square tests to examine concordance in test results within couples and the secondary outcomes listed a)-i). The acceptability of self-sampling for STI testing by men and women will be examined using responses to Likert scales asked as part of the couple’s health screening questionnaire, separately for men and women, and compared within couples.

The content of the intervention is designed to enhance couples’ levels of communication, intimacy, and other positive relationship characteristics. Therefore, we expect that as couples’ levels of positive relationship characteristics increase, they will be more likely to participate in couples HIV testing. To evaluate the extent to which relationship dynamics are associated with couples’ uptake of HIV testing together, we will describe the change in relationship scores between baseline and 4-weeks, and baseline and 4-months. We will test for associations between these score changes and the HIV couples testing outcome using logistic regression. In addition, the acceptability of the intervention and study participation will be explored through thematic analysis using findings from individual, semi-structured process interviews, and descriptive statistics of responses to the process evaluation questions asked of all participants as part of the 4-month questionnaire.

DNA yield from stored penile swabs will be used to determine whether men’s self-sampling around the coronal sulcus is a feasible method for sample collection, an important finding for future studies. Assuming sufficient DNA for 16S analysis and protein for proteomic analysis from the stored swabs, vaginal and penile microbiome composition will be described. For functional analysis, iBAQ values of proteins with the same Gene Ontology IDs will be aggregated. Basic R functions and the ggplot2 R package will be used for data manipulation, transformation, normalisation and generation of graphics. Data will be further explored using principal component analysis using the mixOmics R package, unsupervised hierarchical clustering using the Complex Heatmap package and FlipPlots. The limma R package will be used to identify differentially abundant taxa, proteins and gene ontologies within couples and between groups defined by age, STI status, and 16S profiles.

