### Study objectives

The primary objective of the Igugu Lethu study is to measure the efficacy of our optimised theory-based and culturally appropriate couples-focused intervention on the uptake of HIV testing as a couple. We also have four secondary objectives. First, we aim to investigate the extent to which relationship dynamics are factors in achieving the outcome of couples’ uptake of HIV testing together. Second, we aim to explore whether couples take up other testing opportunities offered during the health screening visit, and the frequency of couples’ health concordance (the same status) for the different tests conducted. Third, we aim to identify operational reasons for failure or success in implementing the intervention and of the study as a whole. Finally, we aim to explore the penile microbiome functional characteristics of male partners and the vaginal microbiome functional characteristics of female partners and concordance in these characteristics within couples.

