### Study procedures and follow-up

#### Baseline survey

The baseline survey includes measures of domestic violence and mutual disclosure to confirm the couple’s eligibility. In addition, the survey includes measures of relationship domains such as satisfaction, communication and measures about HIV and reproductive health (e.g., fertility intentions, HIV knowledge and risk perception, and sexual behaviour). All measures were previously used in Uthando Lwethu. We have dropped some demographic questions from the Uthando Lwethu baseline questionnaire, which were deemed unnecessary, and added questions on self-reported health status (e.g. raised blood pressure and diabetes) and health behaviours, as recommended by the WHO STEPs protocol [34].

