#### Secondary outcomes of the study

The following secondary outcomes will be measured among couples who participated in the couple’s health screening visit:Concordance of HIV test results among couplesUptake of blood pressure (BP) measurement as a coupleConcordance of hypertension diagnosis (defined as > 140/90 mmHg) within couples who take up couple’s BP measurementsUptake of sexually transmitted infection (STI) testing as a coupleConcordance of STI test results within couples who take up couple’s STI testingUptake of random blood glucose (RBG) finger-prick test for diabetes as a coupleConcordance of diabetes diagnosis (defined as RBG > 11.0 mmol/L) within couples who take up the couple’s RBG testingUptake of height and weight measurement for the calculation of body mass index (BMI) as a coupleObesity (BMI ≥ 30 kg/m2) concordance within couplesAcceptability of self-sampling for STI testing, measured using Likert scales asked as part of the couple’s health screening questionnaireDNA yield, and DNA analysis, of the penile swab samples self-collected by men for STI testing, measured using DNA amplification methodsPenile microbiome functional characteristics of male partners using stored penile swabs, assessed using metaproteomics analysesVaginal microbiome functional characteristics of female partners using stored vaginal swabs, assessed using metaproteomics analysesConcordance of results from metaproteomics analyses of penile and vaginal swabs within couples

Additional secondary outcomes are:o.Acceptability of the intervention and study participation using findings from individual, semi-structured process interviewsp.Whether relationship dynamics are factors in achieving the outcome of couples’ uptake of HIV testing together, using relationship scale variables collected at baseline, week 4, and 4 months

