### Statistical considerations

#### Sample size, accrual, follow-up

In the Uthando Lwethu study, 39% of the intervention arm (65/168 couples) had taken up testing together for HIV by 4-months follow-up. A sample size of 180 couples in the Igugu Lethu study provides more than 85% power, at the 5% level, to detect a 40% increase in the proportion testing together, i.e. change from 39 to 55% between the two versions of the intervention, and allow for 5% lost to follow-up or break-up by 4-months.

We aim to accrue the sample of couples over approximately 16 months of active recruitment. Given the continued SARS-CoV-2 pandemic, changes in public health and research-related restrictions may mean a slower rate of recruitment. We will recruit in waves and aim to have approximately 20 couples participate in a round of intervention activities, and will continue to conduct intervention rounds until we achieve our goal of 180 couples. We will follow the couples for a total of 4-months from the date of the first group session in each intervention round.

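### Chi-square tests are named for within-couple concordance and for uptake, but they do not estimate agreement, have too few expected couples for the rarer conditions, and are undefined for the uptake outcomes

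*Protocol article*

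**What the plan says.** The second secondary objective (Study objectives) covers uptake of the other tests and "the frequency of couples’ health concordance (the same status) for the different tests conducted". Concordance therefore means that both partners have the same result.

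Under Secondary outcomes of the study, a lettered list opens by stating that these "secondary outcomes will be measured among couples who participated in the couple’s health screening visit". Counting in list order, a, c, e, g and i are concordance of HIV, hypertension, STI, diabetes and obesity. Outcomes b, d, f and h are uptake, as a couple, of blood pressure measurement, STI testing, glucose testing, and height and weight measurement.

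The Data analysis section first says of uptake: "We will also consider the proportion of couples taking up each of the other non-HIV tests offered". The next sentence plans descriptive statistics and says the team will "apply chi-square tests to examine concordance in test results within couples and the secondary outcomes listed a)-i". The section names no measure of agreement, no small-sample alternative, and no comparator for the uptake outcomes. The historical comparison it describes is for couples HIV testing only.

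**The concern.** Three things do not fit together.

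- **Estimand.** The objective asks how often partners share a status. A chi-square test asks whether one partner's status is independent of the other's. It returns a p-value without a size, and it is two-sided in direction: strong discordance is as significant as strong concordance.
- **Cell counts.** The analysis is confined to couples who attend screening, which is a fraction of 180. For the less common conditions the both-positive cell may be too small for the large-sample test.
- **Scope.** The span a) to i) takes in four uptake proportions measured in one cohort, with nothing to compare them against.

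The stake is how the second secondary objective is reported. A raw concordance percentage beside a chi-square p-value leaves the reader unable to tell agreement beyond chance from agreement that comes only from a condition being rare.

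**Working it through.** **Figure in the plan.** No power or precision is stated for concordance. The only stated figure is for the primary comparison: "A sample size of 180 couples in the Igugu Lethu study provides more than 85% power, at the 5% level". With 168 historical couples, 180 new couples, 39% against 55% and a two-sided 5% level, the usual two-proportion formula gives 85.1%, so the plan's inputs are read here as intended.

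**Screened couples.** The planning scenario is a "change from 39 to 55% between the two versions of the intervention", and the 39% rests on this: "39% of the intervention arm (65/168 couples) had taken up testing together for HIV by 4-months follow-up". The plan allows 5% loss, and 180 × 0.95 = 171.

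- At 39% of 180: 0.39 × 180 ≈ 70
- At 55% of 171: 0.55 × 171 ≈ 94
- At 55% of 180: 0.55 × 180 = 99

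The non-HIV tests are optional at the visit, so for them 70 to 99 is an upper range.

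**Expected both-positive couples.** Under independence E = n × p(women) × p(men). The prevalences are those cited in the Background and Study setting sections and are applied equally to both sexes. The article gives no STI prevalence, so 3% to 10% is an assumption.

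| Condition | Prevalence | n = 70 | n = 94 | n = 99 |
|---|---|---|---|---|
| STI (assumed) | 3% to 10% | 0.1 to 0.7 | 0.1 to 0.9 | 0.1 to 1.0 |
| Diabetes | 10.1% | 0.7 | 1.0 | 1.0 |
| Hypertension | 24% | 4.0 | 5.4 | 5.7 |
| HIV | 29% | 5.9 | 7.9 | 8.3 |

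For example, diabetes at n = 99 is 99 × 0.101² = 1.01. By the usual rule of thumb of at least 5 expected per cell, the prevalence needed in both partners is √(5/n): √(5/99) = 22% to √(5/70) = 27%.

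**Chance concordance.** With equal prevalence p in both sexes it is p² + (1 − p)². For diabetes this is 0.101² + 0.899² = 0.818, so about 82% of couples agree with no link between partners at all.

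**What the test does and does not show.** The tables below each have 99 couples and are illustrative, not predictions. The order is both positive / only the woman / only the man / neither. Kappa = (observed − chance) / (1 − chance). When both sexes have the same prevalence, uncorrected chi-square = n × kappa², so the sign of kappa is lost.

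| Table | Observed concordance | Chance | Kappa | Chi-square | p |
|---|---|---|---|---|---|
| 1 / 9 / 9 / 80 | 81/99 = 81.8% | 81.8% | 0.00 | 0.00 | 0.99 |
| 16 / 14 / 14 / 55 | 71/99 = 71.7% | 57.8% | 0.33 | 99 × 0.330² = 10.8 | 0.001 |
| 2 / 28 / 28 / 41 | 43/99 = 43.4% | 57.8% | −0.34 | 99 × 0.339² = 11.4 | 0.0007 |

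The last two tables have the same margins (30 of 99 positive in each sex) and nearly the same p-value. In one, partners agree more often than chance; in the other, less often. In the first table concordance is high, and the non-significant test rightly says that this is no more than chance. The p-value alone cannot convey how often partners share a status.

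**Uptake.** Each of b, d, f and h is one count over one denominator. A chi-square test needs either a second group or a null proportion. The article gives neither.

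**The case against.** The strongest reply is that the same sentence also plans descriptive statistics. The objective asks for a frequency, a frequency is descriptive, and so percent concordance can be reported as planned. This stands. A reader might infer that the objective would be answered only with p-values; the text does not support that.

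Second, in a 2×2 table independence is the same null hypothesis as kappa = 0, so chi-square is a legitimate test of no agreement beyond chance where cells are adequate. This also stands. It would be wrong to say that the test has nothing to do with agreement. What is left is that it gives no estimate and no direction.

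Third, moving to an exact test when cells are sparse, or adding kappa, is detail that an analysis plan may hold. That is fair for an omission. Here, however, the article names the method and applies it to the whole span, so the stated method is what needs amending.

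Fourth, the sentence before it already treats uptake as proportions, and the chi-square tests may be meant for concordance only. That is a reasonable reading, but the wording does not make the separation.

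Two stronger inferences should be resisted:

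- One could build an obesity table from the cited 32% prevalence and the 6.5-fold sex ratio and find a significant test with poor agreement. Those figures come from different studies, and such a table also needs assumptions about the sex split and about which partners are paired. It is not a magnitude for this study.
- Because the baseline survey "added questions on self-reported health status (e.g. raised blood pressure and diabetes", one could object that a treated, controlled partner is counted as free of the condition. The article defines these outcomes by measured thresholds and speaks of concordance in tests conducted, so this is consistent. Adding self-report would create a different outcome.

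**Conclusion.** The concern holds as a minor point on secondary outcomes. The named test is a valid null test for HIV, where 5.9 to 8.3 both-positive couples are expected. It is borderline for hypertension (4.0 to 5.7). It is unreliable for diabetes (0.7 to 1.0) and for any STI at 10% prevalence or lower (1.0 or fewer). For none of the conditions does it estimate agreement or show its direction. For the four uptake outcomes it is undefined.

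These sizes rest on 39% to 55% of couples being screened, on equal prevalence in both sexes, and on population prevalences from 2004 and 2011 that may not hold in these couples. The STI range is assumed. The glucose threshold may identify fewer people than the cited diabetes prevalence, which would make that table sparser still. The primary comparison of couples HIV testing is not affected.

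**What to change.** In the Data analysis section, split the sentence in two.

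- **Concordance outcomes (a, c, e, g, i).** Report the four-cell male-by-female table, observed concordance with an exact 95% confidence interval, the concordance expected by chance from the observed margins, and kappa with a 95% confidence interval. If a test of association is wanted, use Fisher's exact test.
- **Uptake outcomes (b, d, f, h).** Report each as a proportion of couples attending the screening visit with an exact 95% confidence interval, and take them out of the chi-square sentence.

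For the diabetes illustration above, the first line would read: 81 of 99 concordant, 81.8% (exact 95% CI 72.8% to 88.9%), 81.8% expected by chance, kappa 0.00. That tells the reader directly that the high figure reflects rarity.

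The cost is analysis wording only. All the data are already to be collected, and neither the sample size nor any study procedure changes.

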#### Couples Counselling sessions

Couples will receive up to four couples’ counselling sessions, each lasting 1 to 2 h. These sessions will be led by a trained counsellor. The sessions include communication skills training, problem-solving, setting health-related relationship goals, and exploring perceived benefits and barriers to HIV testing within the couple. Each session will be spaced approximately 1 week apart at times convenient for couples.

If the couple engages in couples HIV testing at an earlier point in the intervention, the counselling structure will change, such that if a couple tests together after 1–2 counselling sessions, they will be offered one final counselling session, which would include the content of counselling session 4 in terms of planning for their future together.

If a couple misses a session, staff will call each partner to reschedule the appointment. If the couple cannot be reached, and they have consented to being visited at their home, a staff member will go to their home to follow up. If a couple has not completed the intervention sessions within 3-months of group session 1, no further intervention sessions will be arranged for this couple. Based on our experience in the Uthando Lwethu study, if a couple is motivated to take part in the intervention, all sessions will be completed within this 3-month window.

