#### Follow- up

All enrolled couples will have follow-up assessments in person or by phone at 4-weeks and at 4-months after the Group 1 session. The follow-up questionnaires used at 4-weeks and 4-months are similar to the follow-up questionnaire used in the Uthando Lwethu study. Each follow-up visit will follow similar procedures as detailed for the baseline survey. Each member of the couple will be interviewed separately, ideally at the same time, by a gender-matched interviewer.

During the baseline consent process, participants will be asked if they are willing to be contacted by phone for appointment reminders, as well as follow ups for missed appointments. They will also be asked if they are willing to be visited at home if they miss a study visit. After participants have consented to participate in the study, they will be asked to fill out a tracking form. This form will collect contact details, to facilitate reminder calls for scheduled appointments, as well as follow up calls for missed appointments. Additionally, if the participant agreed to be visited at home after missing a study visit, they will provide detailed information about the location of their primary residence, as well as any alternative residences. Contact information will be updated during each follow up visit.

At the end of the 4-month interview, participants will receive a certificate of study completion, an end of study information sheet and they will be asked to provide written consent to contact for future studies.

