#### Couples health screening visit

Couples enrolled in the Igugu Lethu study may schedule an appointment for a couples’ health screening visit at any time after the first group session, once they feel ready to participate in HIV testing and counselling together. The health screening visit will only proceed if, on the appointment date, both partners consent to HIV testing together. All other tests offered are optional. The visit will be conducted to avoid days when the female partner is menstruating. If couples report testing for HIV together as a couple at an alternate venue during the Igugu Lethu study, the couple will be encouraged to undergo the couples health screening visit before completion of study participation.

Informed consent will be taken for each of the health screening procedures (HIV test, random blood glucose (RBG) tests, blood pressure and body mass index (BMI) measurements, and self-sampling for sexually transmitted infection testing) at the start of the visit from each couple by the study counsellor.

At the couples health screening visit, height and weight will be measured, and BMI will be calculated for each partner using an electronic scale (Scale Digital BMI 1110H SOAMAA). Blood pressure will be measured by a study counsellor using Brand Axcess BP 1359 devices while the participant is seated, and three consecutive readings will be averaged [35], in line with recommendations by the American Heart Association.

The counsellor will explain the need for self-collected samples to test for chlamydia, gonorrhoea, and trichomoniasis. The counsellor will explain and demonstrate the procedure for obtaining the self-collected vaginal swabs to the female member of the couple and will ask her to self-collect two sequential vaginal swabs behind a medical curtain for privacy. A nurse will be on call if assistance is needed. For men, the counsellor will explain and demonstrate how to obtain a self-collected penile swab, rotating a flocked swab twice around the full circumference of the penis at the *coronal sulcus*, the junction between the glans and the shaft of the penis. A urine sample will be requested for testing *C. trachomatis, N. gonorrhoeae*, and *T. vaginalis* infections. After the sample collection, samples will be transported to a commercial accredited laboratory in cool boxes. The couples health screening questionnaire includes questions on the acceptability of self-sampling.

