### Outcomes

#### Primary outcome

The primary outcome measure is the proportion of couples that take up couples HIV testing as part of a health screening visit during study follow-up i.e. within 4 months from the date of the first group session, compared to the equivalent proportion in the intervention arm of the Uthando Lwethu study (historical controls).

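### The baseline-to-4-month change in relationship scores is used to explain couples testing, although for nearly all testers that score is taken after they have tested

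*Protocol article*

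**What the plan says.** All references are to the protocol article.

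- **Aim.** Study objectives, first secondary objective, asks how far "relationship dynamics are factors in achieving the outcome" of testing together. Item p under Secondary outcomes repeats this and names the relationship scales at baseline, week 4 and 4 months.
- **Outcome window.** Primary outcome counts testing "within 4 months from the date of the first group session".
- **When couples can test.** Under Couples health screening visit, enrolled couples "may schedule an appointment for a couples’ health screening visit at any time after the first group session".
- **When scores are taken.** Follow-up provides for "follow-up assessments in person or by phone at 4-weeks and at 4-months after the Group 1 session".
- **Model.** Data analysis describes the two score changes (baseline to 4 weeks, baseline to 4 months) and then states: "We will test for associations between these score changes and the HIV couples testing outcome using logistic regression". The same paragraph gives the expected direction: as positive relationship characteristics rise, couples become more likely to test.
- **Counselling after early testing.** Couples Counselling sessions says that for couples who test after one or two counselling sessions, "they will be offered one final counselling session".

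The section does not bring the test date into this model, restrict it to couples not yet tested, or lag the scores.

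**The concern.** The outcome window and the second follow-up survey share a time origin and end together. A couple counted as a tester has, in general, already been tested, counselled and told both results when the 4-month score is taken. The model nevertheless treats the change up to that point as the explanation of testing.

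The protocol gives reasons to expect testing to move the scores. Couples in which both partners have disclosed results to each other are excluded, so testing together will often be the first mutual disclosure. The Risks section lists learning that oneself or one's partner is positive as a risk, and says that taking part may cause tension or conflict. Early testing also changes the counselling that follows, which is a possible second route from testing to later scores.

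What is at stake is the reading of the intervention's proposed mechanism. A positive 4-month association could be reported as support for it when it reflects the effect of testing. If testing strains relationships, a real contribution of relationship dynamics could be hidden or reversed.

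**Working it through.** The protocol gives no figure for this analysis, so there is none to reproduce. The inputs below come from its timing statements and its sample-size section.

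**1. Order of events (week 0 = group session 1)**

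| Event | Time | Source |
|---|---|---|
| Testing can begin | just after week 0 | Couples health screening visit |
| Group session 2 | about week 1 | Group session 2 |
| Counselling sessions 1–4 | about weeks 2, 3, 4, 5 | weekly spacing in Couples Counselling sessions; the start one week after group session 2 is my assumption |
| First follow-up score | week 4 | Follow-up |
| Outcome window closes | month 4 | Primary outcome |
| Second follow-up score | month 4 | Follow-up |

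*4-month change:* the score is taken as the window closes, so it follows testing for nearly every tester who has one. Exceptions are surveys done slightly early or at about the time of the test.

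*4-week change:* it precedes testing for couples who test after week 4 and follows it for those who test before. Testing after one or two counselling sessions, about weeks 2–3, is expressly foreseen.

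**2. Couples affected in the 4-month model**

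- Couples with a 4-month score: 180 × (1 − 0.05) = 171 (5% loss or break-up, sample-size section).
- Testers at the planned 55%: 0.55 × 171 = 94.05, about 94.
- Testers if uptake stays at the historical 39%: 0.39 × 171 = 66.7, about 67.

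This assumes that loss is unrelated to testing. It counts couples whose order is reversed; it does not measure bias.

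**3. How far reversal alone could mislead**

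The planned regression was simulated for 171 couples, with one score change per couple (SD 1) and 2,000 replicates per setting. Testing was generated independently of score change. Testing then shifted later scores by d SD. The table shows the share of studies with p < 0.05 for the 4-month change, across uptake of 39% and 55%.

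| d (assumed) | Rejection rate | Median odds ratio per SD |
|---|---|---|
| 0 | 4–5% | about 1.0 |
| 0.2 | 23–25% | about 1.22 |
| 0.3 | 45–49% | about 1.35 |
| 0.5 | 86–90% | about 1.66 |

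Simulation error near 5% is √(0.05 × 0.95 / 2000) = 0.5 percentage points. A fall in scores of the same size would mirror these results below an odds ratio of 1.

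For the 4-week change, the result depends on the share of testers who test before week 4. At d = 0.5 the rejection rate was about 11% with a 25% share, 34% with 50%, and 63–67% with 75%. At d = 0.2 it was about 6–7%, 9–10% and 14–17%.

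Relating the 4-week change to later testing, among couples untested at week 4, gave 4–6% rejection and a median odds ratio of about 1.0 in every setting. The artefact disappears once the order is respected.

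The documents give neither the shifts nor the early-testing shares. All are assumptions, shown as a range.

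**The case against.** The strongest defence is that the plan claims only association. The analysis is one of many secondary outcomes, carries no power statement or decision rule, and leaves the primary comparison untouched. Baseline scores are already listed among the variables for this objective, and an unseen analysis plan might add an ordering by test date. The simulated error rates rest on assumed shifts.

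Most of this is fair, and it limits the weight of the point. It does not remove it. The section names predictors, outcome and model, so the ordering is stated, not left open. The objective and the expected direction both treat relationship change as coming before testing. Listing baseline scores does not reorder the 4-month change.

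Some stronger readings are tempting but not supported:

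- **Both score changes follow testing.** For couples who test after week 4, the 4-week change does precede testing. Sessions are only approximately weekly, are arranged at the couples' convenience and may run to 3 months, so the share testing before week 4 cannot be derived.
- **Every one of the 99 testers (0.55 × 180) is affected.** This ignores the planned 5% loss. Follow-up also ends at break-up, so some testers will have no 4-month score.
- **The historical study shows the size.** Its 65 of 168 couples tested by 4 months and 42% by 9 months say nothing about test order relative to a survey, or about testing changing scores.
- **Change scores without baseline adjustment bring regression to the mean.** The article lists no covariates for this model, and silence in a condensed article does not show that the baseline score is left out.
- **Shorter counselling after early testing changes the scores.** The altered schedule is documented; its effect on scores is not.

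**Conclusion.** The point holds for the baseline-to-4-month change. As written, that model cannot show whether relationship dynamics contribute to testing, because the predictor is measured after the outcome for nearly all testers who have it: about 94 of 171 couples at the planned uptake. This rests on the protocol's own timing and on the assumption that the outcome in this model is testing within 4 months.

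For the baseline-to-4-week change, the same fault applies only to couples who test before the 4-week survey. The protocol foresees such couples but gives no number.

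The size of any bias is unknown. It depends on how much testing moves later scores; the simulation shows that a shift of 0.2 to 0.5 SD would be enough to matter. The analysis is secondary, so this should be corrected before analysis but does not threaten the primary result.

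**What to change.** Reword the relationship-dynamics paragraph in Data analysis as follows.

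1. Do not use the baseline-to-4-month change to explain testing. Report it descriptively, or analyse the 4-month score as an outcome, comparing testers with non-testers and adjusting for baseline score.
2. Use baseline relationship scores as predictors of testing within 4 months.
3. Use the 4-week score, adjusted for baseline score, as predictor of first couples testing after the 4-week survey and up to 4 months, among couples not yet tested at that survey. Describe earlier testers separately.

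A time-to-testing model with scores as time-varying covariates is a reasonable alternative to step 3.

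No new data collection should be needed: the surveys are planned, and the outcome definition already requires test dates relative to group session 1. The price is fewer events in step 3 and a conclusion limited to later testers. With 94 testers among 171 couples, if 25%, 50% or 75% of testers test before week 4, about 71, 47 or 24 events remain among about 147, 124 or 100 couples (171 minus the early testers). These shares are assumptions.
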